**Methods:**

This is an assessor- and participant-blinded, two-arm, pragmatic, comparative effectiveness non-inferiority randomised controlled trial (RCT) conducted in Australia. We are recruiting 394 people from the community with chronic knee pain consistent with a clinical diagnosis of knee OA. Participants are randomly allocated to receive physiotherapy care via i) video-conferencing or; ii) face-to-face consultations. Participants are provided five consultations (30–45 min each) with a physiotherapist over 3 months for prescription of a home-based strengthening exercise program (to be conducted independently at home) and physical activity plan, as well as OA education. Participants in both groups are provided with educational booklets and simple exercise equipment via post. The co-primary outcomes are change in self-reported i) knee pain on walking; and ii) physical function, with a primary end-point of 3 months and a secondary end-point of 9 months. Secondary outcomes include changes in other clinical outcomes (health-related quality of life; therapeutic relationship; global ratings of change; satisfaction with care; self-efficacy; physical activity levels), time and financial costs of attending consultations, healthcare usage and convenience. Non-inferiority will be assessed using the per-protocol dataset.

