The primary aim of this RCT is to determine if video-conferencing consultations are non-inferior to face-to-face consultations with a physiotherapist for improving knee pain on walking and/or physical function at 3 months (primary time-point) and 9 months (secondary time-point), in people with knee OA. We hypothesise that video consultations are not inferior for improving knee pain on walking and/or physical function compared to face-to-face care in people with knee OA. Secondary aims are to compare the clinical effectiveness (health-related quality of life, therapeutic relationship, global ratings of change, satisfaction with care, self-efficacy, physical activity levels), cost-effectiveness (participant-level travel time and travel-related costs, health care usage) and convenience of video-conferencing consultations to face-to-face consultations, as well as explore potential moderators of treatment effect.

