### Sample size calculations

Sample size is based on detecting non-inferiority of video consultations relative to face-to-face at 3 months after randomisation. For change in NRS pain, a non-inferiority margin (NIM) of 0.95 units was chosen as this is less than the lowest of the range (1.0–2.0 units) [46, 47] reported as the minimum clinically important difference (MCID) by people with chronic pain, and less than the MCID of 1.75 units (extrapolated from a 100 mm visual analogue scale (VAS)) [48] for OA by clinician consensus. For change in WOMAC subscales, a NIM of 8 mm on VAS versions of WOMAC (score 0–100) is used in drug non-inferiority RCTs [49], as it is less than the MCIDs of 9.1–9.3 mm [50, 51]. We are using the Likert version of WOMAC (scored 0–68) for function, thus our NIM for change in function is 5.44 units (extrapolated from 8 mm). Assuming standard deviations (SD) of changes from baseline of 2.8 and 15 units for pain and function respectively and correlations of 0.3 between baseline and follow-up [11, 26], 15% loss to follow-up, 90% power, and a one-sided 2.5% significance level, we need 197 people/arm for change in pain and 172/arm for change in function, a total of 394 people.

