Consistent with OARSI guidelines [52], non-inferiority will be assessed using the per-protocol dataset (including only those randomized participants who attended ≥3 consultations). Between-group differences in mean change in pain and function (baseline minus follow-up) will be compared using linear regression modelling adjusted for baseline and the stratifying variable of physiotherapist. If a physiotherapist treats participants at two locations, two separate terms for that physiotherapist, corresponding to each location, will be included. Non-inferiority will be demonstrated if the lower bound of the two-sided 95% CI for between-group difference (video-conferencing minus face-to-face) is above − 0.95 for change in pain and/or − 5.44 for change in function, at 3 months. 95% CIs correspond to testing the null hypothesis of non-inferiority at a one-sided significance level of 2.5%. Due to difficulties with their interpretation, *p*-values associated with non-inferiority hypotheses are not commonly reported and will not be reported here [53]. Multiple imputation will be used to impute missing data, and an intention-to-treat analysis (including all participants in their randomised groups) will be conducted to help assess robustness of conclusions (sensitivity analysis). Given that participants with knee OA seek physiotherapy care for different reasons, we will interpret and report findings transparently and separately for each co-primary outcome. For example, if we demonstrate non-inferiority of video consultations with respect to function but not pain, we will conclude that video consultations are non-inferior to face-to-face care for improving function but are inferior for pain relief in people with knee OA. Patients seeking care, and physiotherapists delivering care, will then be fully informed about benefits, and limitations, of video consultations compared to face-to-face care with respect to the different co-primary outcomes. If non-inferiority of a co-primary outcome is demonstrated, superiority of the outcome will then be assessed using the intention-to-treat dataset and declared if the lower bound of the two-sided 95% CI for between-group difference exceeds zero.

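### Non-inferiority is decided only among participants who attended at least three consultations, and the intention-to-treat result cannot overturn the claim

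*Protocol article*

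**What the plan says.** The Statistical analysis plan section names the deciding population: "non-inferiority will be assessed using the per-protocol dataset (including only those randomized participants who attended ≥3 consultations". The abstract says the same: "Non-inferiority will be assessed using the per-protocol dataset". The decision rests on a single confidence bound: "Non-inferiority will be demonstrated if the lower bound of the two-sided 95% CI for between-group difference (video-conferencing minus face-to-face) is above" −0.95 for pain and/or −5.44 for function, at 3 months. These are the margins set under Sample size calculations ("a non-inferiority margin (NIM) of 0.95 units was chosen"; "our NIM for change in function is 5.44 units").

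Missing data are to be multiply imputed, and the analysis of everyone as randomised has a supporting role: "an intention-to-treat analysis (including all participants in their randomised groups) will be conducted to help assess robustness of conclusions (sensitivity analysis". No sentence requires that analysis to clear the margin, and none says what is concluded if the two analyses disagree. The same section opens by presenting itself as the a priori plan, so this is a rule the document states, not a detail it leaves elsewhere.

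Three other places bear on the point:

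- Attendance at consultations is recorded over the three-month intervention and listed among the secondary outcomes.
- Mode of physiotherapy delivery has face-to-face participants paying for their own travel, and encourages video participants to set up the software themselves.
- The aims at the end of the Background include comparing the "convenience of video-conferencing consultations to face-to-face consultations".

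**The concern.** Whether someone reaches three consultations is known only after allocation. If the mode influences who stops early, the people left in the two arms are no longer comparable through randomisation. Someone who stops because video did not suit them leaves the deciding dataset, and so does someone who stops because the travel was too much. In a pragmatic comparison of two modes of delivery, both are part of the answer.

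The randomised comparison is planned, but it cannot change the verdict. A per-protocol bound just above the margin yields a claim of non-inferiority even where the intention-to-treat bound lies below it. The claim is intended to inform service models and funding, so the article should say in advance which result prevails.

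**Working it through.** **1. Reproduce the plan's own figure.** Inputs from Sample size calculations: SD of change 2.8 (pain) and 15 (function), baseline to follow-up correlation 0.3, margins 0.95 and 5.44, one-sided 2.5%, 90% power, 15% loss.

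n per arm = 2 × (1.960 + 1.282)² × SD² × (1 − 0.3²) / margin²

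- Pain: adjusted SD = 2.8 × √0.91 = 2.671; n = 166.1, so 167; 167 / 0.85 = 196.5, so 197.
- Function: adjusted SD = 15 × √0.91 = 14.31; n = 145.4, so 146; 146 / 0.85 = 171.8, so 172.

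Both match the stated 197 and 172 per arm. The sample size is not in question. It does allow only for loss to follow-up, not for per-protocol exclusions.

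**2. Bias in the deciding set.** Let q_V and q_F be the shares excluded for attending fewer than three consultations, and let low attenders improve D points less than attenders in either arm. Then

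per-protocol difference = all-randomised difference + (q_V − q_F) × D.

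The bias vanishes if the shares are equal or if D = 0. Unequal attendance alone is not enough. The document gives none of q_V, q_F or D, so all three are assumptions.

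**3. False non-inferiority for pain.** Set the true all-randomised difference at −0.95, where the error should be 2.5%. Start from 167 evaluable per arm and remove the excluded:

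SE = 2.671 × √[1/(167(1 − q_V)) + 1/(167(1 − q_F))]

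P(claim) = Φ(bias / SE − 1.960)

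| Excluded, video / face-to-face | D | Bias | SE | P(claim) |
|---|---|---|---|---|
| 5% / 5% | 1.5 | 0 | 0.300 | 2.5% |
| 10% / 5% | 1.5 | +0.075 | 0.304 | 4.3% |
| 15% / 5% | 1.5 | +0.150 | 0.309 | 7.0% |
| 20% / 5% | 1.5 | +0.225 | 0.314 | 10.7% |
| 15% / 5% | 2.5 | +0.250 | 0.309 | 12.5% |
| 20% / 5% | 2.5 | +0.375 | 0.314 | 22.2% |
| 5% / 15% | 2.0 | −0.200 | 0.309 | 0.5% |

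In the 15% / 5% row about 142 and 159 participants remain. Using the SE before exclusions (2.671 × √(2/167) = 0.292) would give 7.4%, which ignores the people just removed.

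**4. The reverse pattern costs power.** With a true difference of 0, 5% / 15% excluded and D = 1.5, the bias is −0.15. Power is Φ((0.95 − 0.15)/0.309 − 1.960) = 74%, against Φ(0.95/0.309 − 1.960) = 87% for the same numbers without bias.

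**5. Cost of requiring both analyses.** Simulation for pain, true difference 0, 167 per arm evaluable, equal exclusion in both arms and no outcome gap:

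| Excluded per arm | Per-protocol alone | Both required | Passes per-protocol, fails intention-to-treat |
|---|---|---|---|
| 0% | 90.2% | 90.2% | 0% |
| 5% | 88.8% | 87.9% | 1.0% |
| 10% | 86.8% | 85.7% | 1.2% |
| 15% | 85.0% | 83.7% | 1.3% |

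This treats the imputed intention-to-treat analysis as carrying the information of the 167 observed participants per arm.

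**The case against.** Per-protocol is a recognised population for non-inferiority, and the article cites a guideline for choosing it. Analysing everyone as randomised can dilute a real difference when people do not receive the treatment, so intention-to-treat alone would not be safer in every respect. The intention-to-treat analysis is pre-specified and imputed, so a disagreement would probably be visible to readers. Exclusions may also be few: the threshold is only three of five, and research staff book the first two consultations. All of this stands. It supports examining both sets, but does not justify letting the selected one decide alone, and visibility does not stop the word 'demonstrated' from applying.

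A reader might infer three stronger points that the document does not support.

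- *That the rule favours video.* The direction is open. Travel at one's own expense could produce more low attenders in the face-to-face arm. The article itself expects easier access by video for people outside major cities, and everyone must have an internet device to enrol. On the other side, it hypothesises that people less confident with technology gain less from video.
- *That the 2.5% error holds in neither set.* Unequal attendance does not disturb the error rate of an analysis of all randomised participants, given valid imputation. The difficulty is that this analysis does not decide.
- *That it is a fault to test superiority in another set* ("superiority of the outcome will then be assessed using the intention-to-treat dataset"). This is conventional. An intention-to-treat lower bound above zero necessarily clears both margins.

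**Conclusion.** The concern holds as a fault in a stated decision rule. Non-inferiority is settled in a subset formed after randomisation, and the comparison that randomisation protects has no binding role. How much this matters cannot be read from the document. Under the assumptions shown for pain, the false-claim rate runs from 0.5% to 22.2% against a nominal 2.5%. With a 1.5-point gap and 5% excluded from face-to-face, it rises from 2.5% to 10.7% as the video exclusion rises from 5% to 20%. These figures show sensitivity and are not predictions: the exclusion shares, the outcome gap and hence the sign of the bias are all assumed. The correction is worth making because it is cheap, not because bias has been shown.

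**What to change.** Add one sentence to the Statistical analysis plan section: non-inferiority for an outcome is declared only if the lower bound of the two-sided 95% interval lies above that outcome's margin in both the per-protocol analysis and the multiply imputed intention-to-treat analysis; if the two disagree, the conclusion is 'non-inferiority not demonstrated'. Record it in the dated amendment log that the section already provides for, before unblinding.

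Both analyses are already planned, so no new data are needed. The cost is about one percentage point of power beyond what per-protocol exclusion already takes, for example 86.8% to 85.7% for pain at 10% exclusion. The sponsor may separately wish to keep 90% power in the per-protocol set for pain. That would need 167 / (0.85 × (1 − exclusion)), or 207, 219 or 232 per arm at 5%, 10% or 15% exclusion. The requirement comes from the per-protocol choice itself and not from this change.

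### The plan's worked example turns a failed non-inferiority test into a conclusion of inferiority, and the null hypothesis is misnamed

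*Protocol article*

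**What the plan says.** All the text at issue is in the protocol article's Statistical analysis plan section.

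- **Direction.** "Between-group differences in mean change in pain and function (baseline minus follow-up") are compared, so a positive change is improvement and a negative difference means video did worse.
- **Criterion.** "Non-inferiority will be demonstrated if the lower bound of the two-sided 95% CI for between-group difference (video-conferencing minus face-to-face) is above" a limit set for each outcome. The limits are -0.95 (pain) and -5.44 (function), joined by and/or, and they apply at 3 months.
- **Null hypothesis.** The section states that "95% CIs correspond to testing the null hypothesis of non-inferiority at a one-sided significance level of 2.5"%.
- **Conclusion after a mixed result.** The trigger is worded "if we demonstrate non-inferiority of video consultations with respect to function but not pain, we will conclude". The conclusion drawn about video care is then worded "are non-inferior to face-to-face care for improving function but are inferior for pain relief".

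The example sets no condition on the upper confidence bound, and the section has no inconclusive category. For superiority, by contrast, it requires a 95% interval wholly above zero.

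**The concern.** The test asks whether a deficit as large as the margin can be ruled out. If the lower bound is at or below the margin, the answer is that it cannot. The same interval may still contain zero, and even values that favour video. Calling that outcome inferior treats absence of evidence for one claim as evidence for the opposite claim.

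The misnamed null points the same way. Under the lower-bound rule the null is that video is worse by at least the margin, and non-inferiority is the alternative. A reader who takes non-inferiority as the null could see a missed bound as a rejection of it.

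This is the pre-stated interpretation of the co-primary outcomes. The section says these conclusions will inform patients and physiotherapists, and the Discussion says such evidence should drive funding policy. The Discussion also explains that power is set high so that a non-inferior treatment is not missed by chance. That concedes that a failed test can come from a non-inferior treatment, which the example would nevertheless call inferior.

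**Working it through.** **Inputs (Sample size calculations).** For pain, "a non-inferiority margin (NIM) of 0.95 units was chosen". For function, "our NIM for change in function is 5.44 units (extrapolated from 8 mm"). The variability is given in these words: "Assuming standard deviations (SD) of changes from baseline of 2.8 and 15 units for pain and function respectively". The correlation between baseline and follow-up is 0.3, loss to follow-up 15%, power 90%, and the one-sided level 2.5%. A true difference of zero is not stated; it is assumed here because it reproduces the stated sizes.

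**1. Reproduce the plan's sample size.** n per arm = 2 × SD² × (1 - 0.3²) × (1.960 + 1.282)² / margin², rounded up, then divided by 0.85 and rounded up.

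- Pain: 166.1, so 167; 167/0.85 gives 197.
- Function: 145.4, so 146; 146/0.85 gives 172.

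Both match the protocol. Without the factor (1 - 0.3²) the results are 216 and 189, so the plan applied 0.91 to the variance of change.

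**2. Planned precision.** Analysed per arm = 197 × 0.85 = 167.45. SE = SD × √0.91 × √(2/167.45).

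| | SE | 95% half-width | Criterion fails at or below | CI still contains 0 above |
|---|---|---|---|---|
| Pain | 0.292 | 0.572 | -0.95 + 0.572 = -0.378 | -0.572 |
| Function | 1.564 | 3.065 | -5.44 + 3.065 = -2.375 | -3.065 |

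Between the last two columns lies the inconclusive band: about -0.57 to -0.38 for pain and -3.07 to -2.37 for function. For example, a pain estimate of -0.45 has a CI of about -1.02 to +0.12. It excludes neither zero nor the margin, yet the plan's wording would call it inferior.

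**3. How often, if the arms are truly equal.** P(criterion fails) = 1 - Φ(margin/SE - 1.96).

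- Pain: 1 - Φ(3.254 - 1.960) = 9.8%.
- Function: 1 - Φ(3.479 - 1.960) = 6.4%.

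An upper bound below zero occurs in 2.5% of such trials for each outcome. So 9.8 - 2.5 = 7.3 points for pain and 6.4 - 2.5 = 3.9 points for function are intervals that contain zero but would carry the label.

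**4. Sensitivity to the meaning of 0.3.** Suppose 0.3 is the raw baseline/follow-up correlation and the two SDs are equal (an assumption; the protocol does not say). Then the variance of change is 2(1 - 0.3) = 1.4 times the raw variance, and the residual SD after baseline adjustment is SD × √(0.91/1.4).

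- Pain: residual SD 2.26, SE 0.247, half-width 0.484. The criterion fails at or below -0.466; with equal arms that is 1 - Φ(3.851 - 1.960) = 2.9%.
- Function: residual SD 12.1, SE 1.322, half-width 2.590. The criterion fails at or below -2.850; with equal arms that is 1 - Φ(4.116 - 1.960) = 1.6%.

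On this reading the pain band shrinks to about -0.48 to -0.47. For function it disappears, because the CI width (5.18) is below the margin (5.44). Instead, function estimates between -2.85 and -2.59 meet the criterion while their whole CI lies below zero. The plan does not address that case either.

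**The case against.** **It is only an example.** The sentence is introduced as an illustration of reporting the two outcomes separately, and it covers one mixed result. The plan does not say what would be concluded if both outcomes failed. That limits the literal reach. Still, the sentence commits the trial to a conclusion, and no other rule covers a failed test.

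**The rates are largely planned type II error.** With 90% power, about 10% of trials of equal treatments fail for pain by design. This is true. The objection here is to the label given to those failures, not to their number. The rates also depend on how 0.3 is read, so a range is needed.

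**The misnamed null does no harm by itself.** This stands. The lower-bound criterion, the 2.5% level and the sample size are all correct for the proper null.

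**Stronger readings that the document does not support.** A reader might infer that even an estimate near zero would be reported as inferior. At planned precision it would pass: pain fails only at about -0.38 or worse. A reader might also infer that the plan claims inferiority as proven. It states a conclusion, not a proof, and its Study design section commits to CONSORT reporting for non-inferiority trials.

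**What counts as inferior is a choice.** An upper bound below zero is one standard; an upper bound below the margin is stricter. Either can be pre-stated. The rule must also say what happens when the whole CI lies between the margin and zero, or two labels would apply at once.

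**Conclusion.** The point holds as an error in a pre-stated interpretation. The worked example equates non-inferiority not shown with inferiority, and nothing else in the protocol corrects it. The misnamed null is a separate wording error.

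On the plan's own formula, the mislabelled results are pain estimates of about -0.57 to -0.38 and function estimates of about -3.07 to -2.37. With equal arms, the label would be applied in about 10% of trials for pain and 6.4% for function, or about 3% and 1.6% on the alternative reading of the correlation. These figures extend the example's wording to every failed test on either outcome. They assume normality, the protocol's SDs, 15% loss and about 167 analysed per arm. The primary dataset is per-protocol (at least three consultations attended) and could be smaller, which would widen the intervals and raise the rates.

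**What to change.** Amend the Statistical analysis plan section as follows.

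1. Name the null hypothesis as: video is worse than face-to-face by at least the margin.
2. Replace the worked example with a full rule, applied to each co-primary outcome separately:
   - Lower bound above the margin: non-inferior. If the upper bound is also below zero, report non-inferior by the margin, although statistically worse.
   - Lower bound at or below the margin: non-inferiority not demonstrated. In that case use the word inferior only if the upper bound is below zero; otherwise call the result inconclusive.

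The cost is a few sentences, entered as a dated amendment in the log that the section already provides for. Data collection, margins, analysis model and the sample size of 394 do not change.

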### Economic evaluation

A health economist will oversee assessment of incremental direct and indirect costs of video consultations compared to face-to-face. Primary evaluation will be between-group difference in knee-related health care costs and quality-adjusted life years (QALYs) using generalised linear models to adjust for baseline. Non-inferiority in QALYs will be demonstrated if the lower bound of the two-sided 95% CI for between-group difference of the AQoL-6D is above − 0.08 (half a SD). If one type of consultation is superior but costs more, QALYs will be calculated using area under the curve over 9 months. The incremental cost per QALY as the ratio of difference in mean cost to difference in mean QALYs, and net benefits as the difference in QALYs times the social value of a QALY minus the difference in cost, will then be calculated. If non-inferiority of QALYs is demonstrated, then inferiority in terms of cost (and net benefits) will then be assessed if the lower bound of the two-sided 95% CI for between-group difference exceeds zero. In a secondary analysis, the cost of patient time will be included as an additional cost component.

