#### Secondary outcomes

For quality of life, physical activity and self-efficacy, change scores are calculated using data measured at baseline, 3 months and 9 months. Other secondary outcomes are measured at time-points as indicated below:

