#### Health-related quality of life

Health-related quality of life is evaluated using the Assessment of Quality of Life (AQoL) (version AQoL-6D) [40]. The AQoL-6D contains 20 items that assess independent living, mental health, relationships, pain, coping and senses. Total scores range from − 0.04 to 1.00, with higher scores indicating better quality of life.

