Secondary outcomes will be assessed using data from all participants (i.e. the intention-to-treat sample) and confidence intervals will be interpreted using the superiority framework since we have not pre-defined any NIMs for these outcomes. Linear regression models will be fit to compare continuous outcomes; proportional odds models to compare improvement based on global change; and Poisson or negative binomial regression models to compare count outcomes as appropriate. Assumptions will be assessed using standard diagnostic plots and methods. Since these are all secondary analyses, *p*-values for these assessments will not be adjusted for multiple comparisons [54, 55]. In addition, the outcomes of participant time, physiotherapist time and travel time will be compared between treatment groups using the superiority framework, similarly to other secondary outcomes.

Irrespective of the outcomes of the non-inferiority analysis, we will conduct exploratory analyses to evaluate moderation of the effect of video-conferencing versus face-to-face consultations on primary outcomes by pre-specified potential moderators, i) experience with online video platforms; ii) geographical residence; iii) beliefs about physiotherapy care delivery; and iv) confidence using technology. This will be assessed by including appropriate interaction terms between the moderators and the intervention term, where the superiority framework will be applied for interpreting results. The a priori hypotheses to be tested are:
i.Participants who are less frequent users of video platforms will have less improvement in primary outcomes with video consultations (relative to face-to-face), compared to participants who are more frequent users.ii.Participants who don’t live in major city areas will report greater ease of access, and reduced participant-level time and financial costs (secondary outcomes) with video consultations (relative to face-to-face), compared to participants who live in major cities.iii.Participants who believe that video consultations are less effective for managing musculoskeletal problems will report less improvement in primary outcomes with video consultations (relative to face-to-face), compared to those who believe video consultations are more effective.iv.Participants who are less confident with using technology will report less improvement in primary outcomes with video consultations (relative to face-to-face), compared to participants who are more confident.

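### The economic plan draws a QALY conclusion from an AQoL-6D score difference, and ties its only stated QALY calculation to one result although other steps need it

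*Protocol article*

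**What the plan says.** All references are to the protocol article.

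- **Economic evaluation, primary comparison.** "Primary evaluation will be between-group difference in knee-related health care costs and quality-adjusted life years (QALYs) using generalised linear models to adjust for baseline". No condition is attached.
- **Economic evaluation, non-inferiority rule.** "Non-inferiority in QALYs will be demonstrated if the lower bound of the two-sided 95% CI for between-group difference of the AQoL-6D is above" −0.08, glossed as half a SD. The quantity compared with the margin is the AQoL-6D, and the sentence gives no time-point.
- **Economic evaluation, QALY calculation.** "If one type of consultation is superior but costs more, QALYs will be calculated using area under the curve over 9 months". The cost-per-QALY ratio and net benefit follow from that sentence. Net benefit is defined as "net benefits as the difference in QALYs times the social value of a QALY minus the difference in cost".
- **Economic evaluation, step after non-inferiority.** "If non-inferiority of QALYs is demonstrated, then inferiority in terms of cost (and net benefits) will then be assessed".
- **Secondary outcomes and Health-related quality of life.** The AQoL-6D is a secondary outcome scored from −0.04 to 1.00, "with higher scores indicating better quality of life". On timing: "For quality of life, physical activity and self-efficacy, change scores are calculated using data measured at baseline, 3 months and 9 months".
- **Statistical analysis plan, secondary outcomes.** "confidence intervals will be interpreted using the superiority framework since we have not pre-defined any NIMs for these outcomes".

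**The concern.** Three statements do not fit together.

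1. The non-inferiority conclusion is worded in QALYs, but the test is on a score. The AQoL-6D is a utility at one moment. A QALY, as the same section computes it, is that utility accumulated over nine months. A report that followed the rule would state a QALY conclusion that had not been tested.
2. The section describes how QALYs are calculated only when it discusses one mode being better but dearer. The primary comparison needs QALYs in every case. So does the net-benefit step after non-inferiority, since net benefit contains the QALY difference. Non-inferiority is also the result the trial hypothesises for its clinical outcomes, so the branch without a stated QALY calculation may well be the one used.
3. One section says no margins exist for secondary outcomes, and the next sets a margin for one of them.

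The stake is the cost-effectiveness claim, which is a stated secondary aim. As written, two analysts could report different quantities under the same label, and the choice between them could be made after the results are known.

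**Working it through.** **The plan's own figure.** Economic evaluation gives one number, the margin of −0.08, equal to half a SD. The implied SD is 0.08 / 0.5 = 0.16 on the AQoL-6D scale. The section does not say which SD this is, so 0.16 is an inference.

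**Step 1: from AQoL-6D to QALYs.** Visits are at 0, 0.25 and 0.75 years. By the trapezoidal rule,

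QALY = 0.25 × (u0 + u3)/2 + 0.50 × (u3 + u9)/2 = 0.125·u0 + 0.375·u3 + 0.25·u9.

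The weights sum to 0.75, the most that nine months can yield at a utility of 1.

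**Step 2: what a score deficit of 0.08 means in QALYs.**

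| Pattern of the 0.08 deficit | Calculation | QALY difference |
|---|---|---|
| At 3 and 9 months, equal baselines | 0.08 × (0.375 + 0.25) | −0.05 |
| Held from day 0 | 0.08 × 0.75 | −0.06 |
| At 3 months only | 0.08 × 0.375 | −0.03 |
| At 9 months only | 0.08 × 0.25 | −0.02 |

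No pattern gives −0.08 QALY. The same score difference maps to anything from −0.02 to −0.06 QALY depending on its timing, so a score test at one visit does not settle the QALY question.

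**Step 3: half a SD on the QALY scale.** Assume SD 0.16 at each visit and a common correlation r between visits. Then

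Var(QALY) = 0.16² × [0.125² + 0.375² + 0.25² + 2r(0.125×0.375 + 0.125×0.25 + 0.375×0.25)] = 0.0256 × [0.21875 + 0.34375·r].

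- r = 0.3: SD 0.091, half a SD 0.045
- r = 0.5: SD 0.100, half a SD 0.050
- r = 1.0: SD 0.120, half a SD 0.060

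The half-SD rule carried over to QALYs would therefore give 0.045 to 0.060. The correlations are assumptions. This shows the scale and does not justify a margin.

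**Step 4: where QALYs are needed and where their calculation is stated.**

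| Step in Economic evaluation | Needs a QALY difference? | Calculation stated there? |
|---|---|---|
| Primary comparison | Yes | No |
| Non-inferiority test | Yes, by its label | No, AQoL-6D score used |
| One mode better but dearer | Yes | Yes |
| Net benefit after non-inferiority | Yes, by definition | No |

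**Step 5: does the conflict over margins matter?** The Sample size calculations section implies 167 evaluable per arm for pain: 2 × (2.8 × 3.2415/0.95)² × (1 − 0.3²) = 166.1, rounded up to 167; 167/0.85 = 196.5, rounded up to the stated 197. With SD 0.16, the 95% CI half-width for an AQoL-6D difference is 1.96 × 0.16 × √(2/167) = 0.034. An observed difference between about −0.034 and −0.046 (0.080 − 0.034) would have an interval wholly below zero and wholly above −0.08. At −0.045 the interval is about −0.079 to −0.011. That result reads as worse under the superiority framework and as non-inferior under the economic rule.

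**The case against.** The strongest reply is that the plan remains workable. The primary sentence commits to a QALY comparison without condition. The text on the better-but-dearer case says if, not only if. The AQoL-6D is collected at all three visits in both arms. This stands. A reader might infer that the plan cannot produce its own primary comparison, and the documents do not support that.

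Two other strong readings also fail. One is that passing the non-inferiority test leaves a cost-only evaluation in which a QALY loss is ignored. The text names net benefits at that step, and net benefit includes the QALY difference. The other is that the margin is in the wrong unit. The margin and the tested quantity are both on the AQoL-6D scale, so the fault lies in the QALY label.

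On the conflict between sections, a superiority reading for clinical reporting can sit beside a non-inferiority reading for the economic evaluation. An interval that excludes zero yet stays above a margin is not a contradiction in itself. That also stands, and it reduces the third issue to an exception that the text should state.

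Finally, the article condenses a fuller plan, which might give the time-point and the handling of QALYs. The missing time-point alone would not be a finding. The mislabelled test and the placement of the QALY calculation do not depend on anything left out, because the published sentences disagree with each other.

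**Conclusion.** The point holds as an internal inconsistency in the economic evaluation. A conclusion labelled as QALY non-inferiority would rest on an AQoL-6D score difference. A deficit equal to the margin at both follow-up visits is 0.05 QALY, or 0.06 if held from day 0, and less if present at one visit only. These conversions assume trapezoidal interpolation and, except for the day-0 case, equal baselines. They do not depend on the SD. The only stated QALY calculation sits in one branch, although the primary comparison and the later net-benefit step need it. The statement that secondary outcomes have no margins is inaccurate for the AQoL-6D.

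Precision is not the problem: with SD 0.16 and 167 per arm, power against −0.08 with no true difference is about 99.5%. The co-primary outcomes and the sample size are unaffected.

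**What to change.** 1. State that 9-month QALYs are calculated by area under the curve from baseline, 3 and 9 months for all participants, whatever the clinical, utility or cost result.
2. Report incremental cost, incremental QALYs and net benefit with confidence intervals in every case.
3. Either rename the −0.08 test as non-inferiority in AQoL-6D utility at a named time-point, or state a margin on the QALY scale and justify it. A conversion such as −0.05 is not a justification in itself.
4. In the secondary-outcome paragraph of the Statistical analysis plan section, except the economic AQoL-6D test from the statement that no margins are pre-defined.

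The cost is a few sentences and a small amount of extra analysis. No new data are needed. The article already provides for a dated log of amendments to the statistical plan. The change should be entered there before any comparison by arm is seen.
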